#### Key and Exploratory Secondary Outcomes

2.10.2

The key secondary outcomes are (1) time from start of surgery to when the patient fulfils indicators of hospital discharge (criteria specified in Table 3), (2) Quality of Recovery (QoR) trajectories, (3) patients' qualitative descriptions of anaesthesia and postoperative recovery, (4) cost per gained quality‐adjusted life‐year (QALY) and (5) safety (adverse events). All other outcomes listed in Table 2 are exploratory, and no multiplicity correction is applied to them. Health economic data will be gathered to capture costs and QALY over a full year to account for seasonal variation, allow short‐term postoperative differences to resolve [20], and support annualised cost‐effectiveness estimates.

**TABLE 2 aas70283-tbl-0002:** Key and exploratory secondary outcomes.

Objectives	Outcomes	Assessment(s)
Key secondary outcomes		
*Evaluate the effect of SA* vs. *GA on early and intermediate recovery*	*Time from start of surgery to when patient fulfils indicators of hospital discharge (criteria specified in* Table 3 *)*	Performed by the discharging orthopaedic surgeon and/or nurse and registered as the time when indicators are fulfilled
*Evaluate the effect of SA* vs. *GA on late postoperative recovery*	*Quality of Recovery (QoR) trajectories*	QoR‐15 at baseline and daily postoperative Day 1–14 and once a week until postoperative day (POD) 35
*Describe patient experiences of anaesthesia and postoperative care*	*Patient's qualitative descriptions of anaesthesia and postoperative recovery*	Semi‐structured interviews with 20–30 participants 14–60 days after surgery
*Evaluate the cost‐effectiveness of SA* vs. *GA*	*Cost per gained quality‐adjusted life‐year (QALY), SA vs. GA*	Quality of life (EQ‐5D‐5L, HOOS/KOOS): questionnaires at baseline, 4 weeks, 6 and 12 months Intervention costs: time, material and personnel across stages of anaesthesia Healthcare consumption (inpatient, outpatient, primary care): administrative data, first year Prescribed medication: administrative data and medical records, first year Productivity and informal care: patient questionnaires at baseline, 4 weeks, 6 and 12 months
*Assess the safety of SA and GA*	*Adverse events (AE) and Serious AE (SAE)*	Reported by study staff (see Safety section), from start of anaesthesia to 3 days post‐surgery
Exploratory secondary outcomes		
Preoperative care and anaesthesia		

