### Sample Size

2.12

The trial will enrol 600 participants (300 per group). This sample size provides 80% power at a two‐sided 5% significance level to detect an absolute difference of 10 percentage points in successful same‐day discharge between groups, with expected success rates of 70% (GA) and 80% (SA). To account for potential loss to follow‐up, the sample size allows for approximately 1% attrition (*n* = 6 participants). The effect size was informed by prior literature, retrospective cohort data and clinical consensus [21].

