### Statistical Analysis

2.14

Analyses will follow the intention‐to‐treat principle. The primary analysis of the primary outcome will compare the proportion of successful same‐day discharge between groups using a chi‐square test (or Fisher's exact test if appropriate). A prespecified adjusted analysis using logistic regression including treatment group, type of surgery and study site as fixed effects will also be performed, consistent with the stratified randomisation; both analyses will be reported. Effect estimates will be reported as risk difference and odds ratio with 95% confidence intervals. Analyses adjusted for other prespecified baseline variables will be performed as appropriate. The full analytical approach is prespecified in the statistical analysis plan, which will be finalised prior to database lock.

Continuous secondary outcomes will be analysed using independent *t*‐tests or non‐parametric alternatives as appropriate, and regression models for adjusted analyses. Repeated‐measures outcomes (e.g., QoR‐15 trajectories) will be analysed using mixed‐effects models including treatment group, time and group‐by‐time interaction, with participant‐level random effects and, where appropriate, site‐level effects. Binary safety endpoints will be analysed using chi‐square/Fisher's exact tests and logistic regression. Time‐to‐event endpoints may be analysed using Kaplan–Meier methods and Cox models where appropriate. A two‐sided significance level of 0.05 will be employed.

An interim analysis of the primary outcome is planned after approximately 300 participants have completed primary endpoint assessment to allow early stopping for both futility and safety. A group sequential design with O'Brien‐Fleming boundaries will be used to preserve the overall two‐sided type I error at 0.05. Exact stopping boundaries will be based on the observed information fraction at the interim analysis.

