### Quality of Recovery‐15 as a Key Secondary Outcome

5.2

QoR‐15 was selected as the principal patient‐reported recovery outcome because it captures a multidimensional construct—physical comfort, emotional state, pain, physical independence and patient support—that is not adequately reflected by single‐item measures such as pain scores alone [28]. QoR‐15 has been validated in multiple languages and surgical populations including outpatient orthopaedic surgery, and has an established minimal clinically important difference [29, 30, 31, 32].

In GASPS, QoR‐15 is administered daily from postoperative Day 1–14 and weekly until Day 35. This extended assessment is a strength of the trial, as most studies have measured QoR‐15 only at 24 h or at hospital discharge [31], similar findings were also identified when reviewing assessment of recovery in research [33]. In both studies, the researchers suggest that recovery should be measured several times during recovery [31, 33]. Patients are willing to report daily on how they experience their recovery, and digital assessment has a higher response rate compared to paper‐based assessment [34, 35]. The repeated‐measures design will enable characterisation of the recovery trajectory and identification of the time point at which any potential between‐group difference appears or resolves. This trajectory‐based analysis addresses the need to move beyond single‐snapshot recovery assessments and to examine quality of care beyond traditional markers of morbidity and/or mortality [17, 36]. To mitigate this, the digital follow‐up platform sends reminders to support frequent QoR‐15 completion. Repeated‐measures outcomes will be analysed using mixed models, which provide valid estimates under the assumption that data are Missing At Random (MAR). Should the proportion of missing data exceed a threshold specified in the SAP, sensitivity analysis using multiple imputation will be performed.

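### The QoR-15 mixed model, as its terms are listed, leaves out the collected baseline QoR-15 and the THA/TKA stratum, which costs precision but does not bias the comparison

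*Protocol article*

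**What the plan says.** Section 2.14 (Statistical Analysis) of the protocol article gives the repeated-measures model, with QoR-15 trajectories as its example: mixed-effects "models including treatment group, time and group‐by‐time interaction", participant-level random effects, and site-level effects on a conditional basis.

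Table 2 (section 2.10.2) sets the assessments: "QoR‐15 at baseline and daily postoperative Day 1–14 and once a week until postoperative day (POD) 35". Table 4 places the baseline QoR-15 ahead of randomisation. QoR-15 is the second of five key secondary outcomes, and section 5.2 calls it the principal patient-reported recovery measure.

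Sections 2.3 and 2.7 stratify randomisation by site and procedure. For the primary outcome, section 2.14 puts both factors as fixed effects in the adjusted logistic model and gives the stratified randomisation as the reason. It also allows adjustment for other prespecified baseline variables, without naming them, and refers to the SAP for the full approach. The SAP is not at hand.

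Section 5.2 describes the purpose of the trajectory analysis as including "identification of the time point at which any potential" between-group difference appears or resolves.

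**The concern.** Two variables that normally belong in this model are absent from its listed terms. A baseline score on the same instrument, taken before randomisation, is usually among the strongest predictors of later scores. Procedure is a randomisation factor, and the same section uses it in the adjusted primary analysis but not here. Site is fixed in one model and optional in the other, without a reason given.

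What is at stake is the width of the interval for the main patient-reported result. The participant random effect does not make up for the missing baseline. It accounts for correlation within a patient, but the treatment contrast is made between patients, and only a predictor of between-patient differences shrinks its standard error.

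**Working it through.** **The plan's own figure.** The protocol states "80% power at a two‐sided 5% significance level", with "expected success rates of 70% (GA) and 80% (SA". The uncorrected two-proportion formula gives

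n = [1.96·√(2·0.75·0.25) + 0.842·√(0.70·0.30 + 0.80·0.20)]² / 0.10² = (1.200 + 0.512)² / 0.01 ≈ 293.2,

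so 294 per arm and 588 in total. Allowing 1% attrition, 588/0.99 ≈ 594, against 600 stated. The figure reproduces. It concerns the primary outcome only; no SD, target difference or power is given for QoR-15. I use 297 per arm (594/2) below.

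**Inputs from the documents.** There are 14 daily and 3 weekly assessments, so K = 17 postoperative time points.

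**Assumptions, not in the documents.** Correlation r of baseline with each postoperative score is 0.3 to 0.5. Correlation ρ between postoperative scores is 0.5 to 0.7 with compound symmetry. Variance is equal over time and no data are missing.

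**Single time point.** Adjusting for baseline multiplies the variance of the treatment difference by 1 − r².

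- r = 0.3: 0.91, a 9% reduction. Without adjustment, the same precision at 300 per arm needs 300/0.91 − 300 ≈ 30 more patients per arm.
- r = 0.5: 0.75, a 25% reduction, or 300/0.75 − 300 = 100 more per arm.

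**Average over the 17 time points.** In SD² units the variance of a patient's mean is V = [1 + (K − 1)ρ]/K. After adjustment it is V − r², so the ratio is 1 − r²/V.

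| ρ | V | r | variance ratio | reduction | SE ratio |
|---|---|---|---|---|---|
| 0.5 | 9/17 = 0.529 | 0.3 | 0.830 | 17% | 0.91 |
| 0.5 | 0.529 | 0.5 | 0.528 | 47% | 0.73 |
| 0.7 | 12.2/17 = 0.718 | 0.3 | 0.875 | 13% | 0.94 |
| 0.7 | 0.718 | 0.5 | 0.652 | 35% | 0.81 |

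The gain is larger for the average because averaging removes within-patient noise, so baseline explains a larger share of what remains.

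**In power terms.** For a steady benefit of 0.2 SD (assumed) and 297 per arm, the unadjusted SE is √(2V/297). This is 0.060 at ρ = 0.5 and 0.070 at ρ = 0.7, giving power of 92% and 82%. With baseline adjustment, power ranges from 87% (ρ = 0.7, r = 0.3) to 99.6% (ρ = r = 0.5).

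**Procedure.** The documents give no QoR-15 difference between THA and TKA, so this loss cannot be put in figures. Leaving a stratification factor out of the model tends to make the standard errors conservative.

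**The case against.** The strongest reply is that the list of terms need not be exhaustive. Section 2.14 permits adjustment for further baseline variables and hands the full approach to an SAP that is not shown. The coding of baseline, the residual structure and the choice of contrast are ordinary SAP content. This stands in part: the protocol does not exclude baseline or procedure, and the SAP may contain both. But the article chose to name the model's terms, and those terms are less complete than the adjusted primary model in the same section.

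Baseline might also enter as the first outcome row. With unconstrained baseline means and a change-from-baseline contrast, the variance at one time point is proportional to 2(1 − r). That is 2/(1 + r) times the adjusted variance, or 33–54% more for r = 0.5 to 0.3. A constrained baseline avoids this. The text does not say which is meant.

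A reader might go further and infer that the QoR-15 result rests on the group-by-time interaction, so that a steady benefit would be missed, or that 17 separate day-by-day significance tests are planned. The documents support neither. The model also has a treatment term and can yield an overall average, window means or daily differences. No section names the interaction as the deciding test, and the time-point aim in section 5.2 describes a trajectory, not a testing rule. Nor is the interaction the weaker choice in general. For an assumed 0.3 SD benefit fading with a 7-day time constant (ρ = 0.5 to 0.6, r = 0.3), the interaction test has 95–98% power, against 34–39% for the unadjusted overall average. What can fairly be said is that the deciding contrast is not named.

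**Conclusion.** The point holds as one of precision. The listed QoR-15 model contains neither the collected baseline score nor procedure, and treats site as optional, although procedure and site are both in the adjusted primary model. Following it would not bias the treatment effect. It would give a variance that baseline adjustment could lower by about 9–25% at one time point, or 13–47% for the postoperative average. Those ranges rest on assumed correlations, compound symmetry for the average, and complete data; higher missingness or another correlation pattern would change them. The cost of omitting procedure is not quantifiable from the documents. The primary analysis and the sample size of 600 are unaffected. The missing deciding contrast is a secondary matter for the SAP.

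**What to change.** In section 2.14 and the SAP, list baseline QoR-15 (as a covariate or through a constrained-baseline model), procedure and site as terms in the QoR-15 model, alongside treatment, time and their interaction. Apply the same baseline adjustment to HOOS/KOOS and EQ-5D-5L, for which baseline values are also scheduled.

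In the SAP, name one contrast as the key QoR-15 result, for example the baseline-adjusted mean difference over a stated window, and label the interaction and daily differences as supportive.

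The cost is wording only. No new data are needed, the article reports that recruitment had not begun at submission, and the SAP is still to be finalised.

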### Embedded Qualitative Study

2.15

A purposive sample of approximately 20–30 trial participants (aiming for at least 10 from each group) will be invited to take part in semi‐structured interviews 14–60 days after surgery. Interviews will explore experiences of anaesthesia, outpatient discharge and postoperative recovery. Interviews will be audio‐recorded, transcribed verbatim and analysed using reflexive thematic analysis with iterative coding and theme development [22, 23].

### Health Economic Evaluation

2.16

A cost‐utility analysis will be performed with effects measured as quality‐adjusted life years (QALYs) derived from EQ‐5D‐5L using Swedish preference weights. Incremental cost‐effectiveness ratios will compare GA versus SA. Costs will include intervention‐related resource use, healthcare utilisation, prescribed medications and productivity losses. Analyses will be conducted from both healthcare and societal perspectives. Deterministic and probabilistic sensitivity analyses will explore uncertainty. Secondary cost‐effectiveness analyses will use successful same‐day discharge and HOOS/KOOS as effect measures.

### Patient and Public Involvement

2.17

Patients and/or the public were not involved in the design of this protocol. Plans for patient‐facing dissemination include a lay summary reported in CTIS and accessible summaries of findings after trial completion.

## Ethics and Dissemination

3

### Ethics Approval and Consent

3.1

The study has received regulatory approval from the Swedish Medical Products Agency (EU CT number: 2024‐520127‐89‐00) following a favourable opinion from the Swedish Ethical Review Authority. The trial complies with Regulation (EU) No. 536/2014.

Informed consent will be obtained by a physician at each participating site. Potential participants will receive both oral and written information about the study during the preoperative anaesthesia assessment or at a dedicated study visit prior to surgery.

Participants will be given time to consider participation and to ask questions before providing written informed consent. Consent will be obtained prior to any study‐specific procedures, including randomisation. Consent includes permission to collect and use study data from medical records and patient‐reported outcomes. No biological samples will be collected for research purposes.

Participants will be informed that participation is voluntary and that they may withdraw from the study at any time without any consequences for their clinical care. Participants may also be asked to provide additional consent for participation in the embedded qualitative study involving semi‐structured interviews.

### Safety Considerations

3.2

Both GA and SA are established standard‐of‐care anaesthetic techniques for THA/TKA. Eligibility criteria select patients suitable for outpatient pathways to minimise risk. Adverse events (AEs) and serious adverse events (SAEs) will be defined and assessed according to standard clinical trial definitions and recorded systematically from anaesthesia start to postoperative Day 3. Predefined adverse outcomes will be captured during follow‐up windows defined in the trial protocol.

### Confidentiality

3.3

Personal data will be processed in accordance with GDPR and Swedish data protection laws. Published results will be reported in aggregate, and no individual participant will be identifiable.

### Dissemination

3.4

Findings will be disseminated through peer‐reviewed journals, presentations at national and international meetings and reporting of summary results in CTIS, including a lay summary. Secondary publications are planned for recovery trajectories, qualitative findings, health economic results and longer‐term outcomes.

### Data Sharing

3.5

Individual participant data will not be publicly available due to privacy and regulatory restrictions. De‐identified data may be made available upon reasonable request to the corresponding author, subject to approval by the sponsor and relevant authorities, and in accordance with applicable data protection regulations.

The SAP and HEAP will be finalised and made publicly available in an open‐access repository prior to database lock and analysis. The statistical code used for the primary analyses will be made available following publication of the results.

## Trial Status

4

At the time of submission, the trial status is: not yet recruiting.

Two sites, Lindesberg Hospital and Hässleholm Hospital, are participating in the study from the start. Additional sites may be added. Protocol versions are as stated on the title page. Recruitment start and end dates will be reported in upcoming reports.

## Discussion

5

The choice of anaesthetic methods in TKA and THA has changed little over the last decades despite reduced hospitalisation. Observational studies and register‐based analyses have suggested advantages for neuraxial anaesthesia in terms of perioperative complications and length of stay [12, 24], yet recent cohort data from ambulatory settings show comparable outcomes regardless of technique [9, 25], and two small randomised trials have even indicated faster recovery with TIVA [13, 14].

GASPS is designed as a pragmatic trial; this means that the study is conducted as close to routine clinical care as possible at centres with established outpatient arthroplasty programmes. This design philosophy has several advantages as it enhances external validity, facilitates recruitment, and ensures that the findings are applicable to implementation. Stratification by site and procedure (THA/TKA) in the randomisation further reduces the risk that site‐level variation in co‐interventions confounds the primary comparison, and sensitivity analyses adjusting for important co‐interventions will be pre‐specified in the SAP.

However, some standardisations are required to maintain features that define modern GA and SA in this context while allowing for variation in elements that do not alter the nature of the techniques [26].

Inclusion and exclusion criteria for this study focus on including all patients that may participate in the study but exclude for safety, unsuitability for either SA or GA, or factors that make successful same day discharge unlikely. Unicompartmental knee arthroplasty is not included in the trial, as it differs from TKA in surgical invasiveness and recovery profile. Preoperative opioid use is one such factor that has been described to increase the risk of unsuccessful same day discharge in the literature, and most Swedish outpatient pathways exclude all patients with higher doses of preoperative opioids [21].

### Choice of Primary Endpoint

5.1

We chose successful same‐day discharge as the primary outcome because it reflects the goal of outpatient arthroplasty pathways and is meaningful to patients, clinicians and healthcare systems. Unlike surrogate measures such as time to first mobilisation or pain scores at a single time point, same‐day discharge integrates multiple domains of recovery—pain control, haemodynamic and respiratory stability, motor function, absence of surgical complications and patient willingness—into a single, pragmatic endpoint. A composite definition requiring no readmission within 48 h was added to guard against premature discharge that merely shifts morbidity to a later time point [4, 16, 27]. The limitations of this endpoint include reasons for not being discharged that are not entitled to medical and patient‐related causes and that there is some subjectivity included in the discharge decision.

### Quality of Recovery‐15 as a Key Secondary Outcome

5.2

QoR‐15 was selected as the principal patient‐reported recovery outcome because it captures a multidimensional construct—physical comfort, emotional state, pain, physical independence and patient support—that is not adequately reflected by single‐item measures such as pain scores alone [28]. QoR‐15 has been validated in multiple languages and surgical populations including outpatient orthopaedic surgery, and has an established minimal clinically important difference [29, 30, 31, 32].

In GASPS, QoR‐15 is administered daily from postoperative Day 1–14 and weekly until Day 35. This extended assessment is a strength of the trial, as most studies have measured QoR‐15 only at 24 h or at hospital discharge [31], similar findings were also identified when reviewing assessment of recovery in research [33]. In both studies, the researchers suggest that recovery should be measured several times during recovery [31, 33]. Patients are willing to report daily on how they experience their recovery, and digital assessment has a higher response rate compared to paper‐based assessment [34, 35]. The repeated‐measures design will enable characterisation of the recovery trajectory and identification of the time point at which any potential between‐group difference appears or resolves. This trajectory‐based analysis addresses the need to move beyond single‐snapshot recovery assessments and to examine quality of care beyond traditional markers of morbidity and/or mortality [17, 36]. To mitigate this, the digital follow‐up platform sends reminders to support frequent QoR‐15 completion. Repeated‐measures outcomes will be analysed using mixed models, which provide valid estimates under the assumption that data are Missing At Random (MAR). Should the proportion of missing data exceed a threshold specified in the SAP, sensitivity analysis using multiple imputation will be performed.

